### Sample size

The purpose of this study is to establish proof of concept and feasibility for a larger clinical trial and the number of participants recruited for this study (*n* = 40) matches that of a recent feasibility trial [36]. This study will therefore establish a proof of concept and allow power calculations for a definitive trial.

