**Design:**

This will be an investigator-initiated, single-site, proof-of-concept, double-blind sham-controlled randomised pilot trial in 40 people with PD. Participants will be randomly assigned on a 1:1 ratio to receive either active or sham transcutaneous cervical VNS. All participants will undergo comprehensive cognitive, autonomic and gait assessments during three sessions over 24 weeks, in addition to remote monitoring of ambulatory activity and falls, and exploratory analyses of cholinergic peripheral plasma markers. The primary outcome measure is the safety and tolerability of multi-dose nVNS in PD. Secondary outcomes include improvements in gait, cognition and autonomic function that will be summarised using descriptive statistics.

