### Participants and eligibility criteria

We aim to recruit 40 PwP in total. This study will be used to establish proof-of-concept and feasibility allowing power calculation for a larger definitive clinical trial. Participants will be over 18 years of age but younger than 76 years of either sex and of any racial or ethnic origin. The age cut-off will be used due to the lack of safety data in older or younger participants. All participants will have a diagnosis of PD, as per the UK Brain Bank Criteria [28] and participants may be Hoehn and Yahr stages I to III [29]. All participants must be on stable medication for the preceding month and anticipated over the next three months, able to walk independently without aid for a minimum of two minutes without rest and able to provide informed consent. Our exclusion criteria include:Parkinson’s disease dementia [30] or significant cognitive impairment as determined by a score of < 21 on the Montreal Cognitive Assessment (MoCA);History of stroke, traumatic brain injury, intracranial aneurysm, intracranial haemorrhage, brain tumour or atypical parkinsonian disorder;An unstable medical condition in the last six months or planned surgeries that may involve implants within the next six months;Prescribed centrally acting anticholinergics (e.g., amitriptyline) or cholinesterase inhibitors;Severe orthopaedic or neurological (excluding PD) pathology that will adversely affect gait;Pain at the nVNS treatment site (e.g., dysesthesia, neuralgia, cervicalgia);Previous use of nVNS stimulator device, including previous participation in nVNS research;Women of childbearing potential or who are pregnant or lactating;Active participation in another interventional trial or exposure to an experimental drug or intervention;Lesion (including lymphadenopathy), previous surgery (including carotid endarterectomy or vascular neck surgery) or abnormal anatomy at the treatment site (open wound, rash, infection, swelling, cut, sore, drug patch, surgical scar[s]);Known or suspected severe atherosclerotic cardiovascular disease, severe carotid artery disease (e.g., bruits or history of TIA or stroke), congestive heart failure, known severe coronary artery disease or prior myocardial infarction;Abnormal baseline electrocardiogram (ECG) within the last year (e.g., second or third-degree heart block, prolonged QT interval, atrial fibrillation, atrial flutter, history of ventricular tachycardia or ventricular fibrillation);Uncontrolled high blood pressure (systolic > 160 mmHg, diastolic > 100 mmHg) after 3 measurements within 24 h;Previous unilateral or bilateral vagotomy;Implanted metal cervical spine hardware, other metallic implants or implantable medical devices such as deep brain stimulator, hearing aid implant, pacemaker, implanted cardioverter defibrillator, cranial aneurysm and/or cranial aneurysm clips, history of facial/orbital/metallic fragments, implanted electronic device, neurostimulator, valve replacements/stents, metallic implants/prostheses) near the stimulation site such as a bone plate or bone screw;History of syncope or seizures (within the last 2 years);Patients with active cancer or are in a recent remission of cancer;Clinically significant hypotension, bradycardia, or tachycardia;Insufficient comprehension of the English language.

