### Secondary outcome measures

#### Gait

Gait and posture will be assessed pre- and post-intervention during a two-minute continuous walk using an instrumented walkway and a small, lightweight, sensor worn on the lower back (AX6, Axivity, York, UK; sampling frequency = 100 Hz, gravitational acceleration =  ± 8 g, and gyroscope full-scale range (dps) = 2000, attached using double sided tape and secured in place using hypafix [BNS Medical Limited, Hull, UK]). The sensor is an inertial measurement unit comprising a tri-axial accelerometer and gyroscope. Participants will walk at a comfortable walking pace around a 25 m circuit inclusive of a 6.1 × 0.6 m instrumented walkway (ProtoKinetics LLC, Havertown, Pennsylvania, 120 Hz). The analysis will focus on dopa-resistant characteristics; namely, step time variability and step length variability [4, 13, 49], and other discrete characteristics representing five domains according to an a priori model of gait in PwP (see Table 2 for details) [50].

**Table 2 Tab2:** Description of the validated model of gait in PwP as described by Lord and colleagues [50]

	Gait domain	Description
Validated model of gait in PwP	Pace	The pace domain is captured by characteristics such as step velocity and step length
	Rhythm	The rhythm domain presents the temporal regulation of gait and the timing of steps such as step time, swing time and stance time
	Variability	The variability domain represents the differences from one step to the next. This domain contains variability gait characteristics such as the variability of step length, step time and stance time
	Asymmetry	The asymmetry domain represents the temporal differences between left and right steps and includes gait characteristics measuring the asymmetry of swing time, step time and stance time
	Postural control	The postural control domain represents the ability to maintain balance during walking with gait characteristics including mean step width

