### Statistical analysis

The main analyses will be descriptive, to inform the design of a future trial. We will analyse the numbers of eligible patients enrolled, rate of recruitment, compliance with the intervention and completion of study assessments. We will ascertain the completeness and acceptability of nVNS and identify any potential barriers. Qualitative data analysis from the focus group will adopt a thematic approach [63] with NVivo (QSR International Pty Ltd. NVivo) software used as a coding tool. Statistical analyses will be conducted using MATLAB (The MathWorks, Inc., Natick, MA, USA), SPSS (IBM SPSS Statistics for Windows, Armonk, NY: IBM Corp) and/or R (http://www.r-project.org/). The outcome data will be summarised using descriptive statistics, including means (and medians), standard deviations, and interquartile ranges. It is expected that non-parametric statistics (e.g., Friedman test) will be used throughout due to the small number of participants in this study. To establish proof of concept for active nVNS treatment, we will compare the median change scores (post–pre assessment) of gait and cognitive outcomes between groups using Mann–Whitney U tests. An exploratory outcome will be a metabolomic analysis of cholinergic markers in blood plasma. We will explore the effects of concentrations of the various targeted small molecule Cho metabolites (Cho inclusive) in plasma on cognitive functions and discrete gait characteristics.

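### The plan claims that 40 patients will establish proof of concept, but its between-arm tests are not tied to its own two focus gait outcomes, and 20 per arm can only look for a signal

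*Protocol article*

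**What the plan says.** The protocol article plans 40 patients ("We aim to recruit 40 PwP in total", Participants and eligibility criteria), allocated 1:1 ("Participants will be randomly assigned on a 1:1 ratio to receive either active or sham transcutaneous cervical VNS", Abstract, Design), so 20 per arm. The only basis given for the number is that it "matches that of a recent feasibility trial" (Sample size). The same section then draws the inference at issue: "This study will therefore establish a proof of concept and allow power calculations for a definitive trial".

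The Statistical analysis section first calls the main analyses descriptive. It then says how the inference will be pursued: "we will compare the median change scores (post–pre assessment) of gait and cognitive outcomes between groups using Mann–Whitney U tests". The outcomes in that sentence are plural and unranked. The purpose attached to these tests is stated in the same place: "To establish proof of concept for active nVNS treatment".

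Elsewhere the article does give a priority. The Gait section states: "The analysis will focus on dopa-resistant characteristics; namely, step time variability and step length variability". The objectives, under Participants and eligibility criteria, name the same two characteristics. In both places they come alongside other discrete gait characteristics, and no cognitive outcome is given a similar place. The abstract mentions no between-arm test: "Secondary outcomes include improvements in gait, cognition and autonomic function that will be summarised using descriptive statistics".

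**The concern.** Matching another trial's size shows nothing about what 20 per arm can establish in this one, so the conclusion in Sample size does not follow from its premise.

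The sentence that defines the proof-of-concept comparison covers gait and cognitive outcomes as a class. As written, a favourable difference on any of them could be reported as proof of concept, although the article has already said which two gait outcomes matter most. A set of null differences could equally be read as evidence against the treatment, when the trial is too small to show that.

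The Discussion says that the results will feed into a larger multi-centre trial. What this pilot may claim therefore matters beyond the pilot.

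**Working it through.** **Inputs from the protocol article.** N = 40, 1:1, so n = 20 per arm. No significance level, power, effect size, SD or precision target is given, so 40 cannot be reproduced from a calculation.

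**Outcome count.**
- Discrete gait (Gait section, Table 2): pace 2, rhythm 3, variability 3, asymmetry 3, postural control 1. Total 12. Table 2 gives examples, so 12 is a reading of the named items and not a fixed list.
- Cognition: power of attention, fluctuating attention, digit vigilance accuracy, One Touch Stockings, Paired Associates Learning, Trail Making A and Trail Making B. Total 7.
- Together 12 + 7 = 19. The free-living walking measures (Ambulatory activity, Table 3) are a separate objective and are left out.

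**Assumptions.** Two-sided 0.05 per test; no true effect for the false-positive figures; equal correlation between all outcomes, from 0 to 0.7; normal data for power. None of these is stated in the article.

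**Chance of at least one nominally positive result when nothing works.** With independent tests this is 1 − 0.95^k. For k = 19, 1 − 0.95^19 = 0.62. For k = 2, 1 − 0.95^2 = 0.098. The correlated cases come from 100,000 simulated sets of equally correlated normal test statistics.

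| Correlation | 19 outcomes | 2 focus outcomes |
|---|---|---|
| 0 | 62% | 9.8% |
| 0.3 | 52% | 9.5% |
| 0.5 | 41% | 8.9% |
| 0.7 | 28% | 8.3% |

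The number of false positives expected among 19 tests is 19 × 0.05 = 0.95, whatever the correlation.

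**Power of one Mann–Whitney test, 20 v 20** (20,000 simulated trials per value, d in SD units of the change score):

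| d | Power |
|---|---|
| 0.3 | 14% |
| 0.5 | 32% |
| 0.8 | 67% |
| 0.9 | 77% |
| 0.95 | 81% |

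So 80% power is reached only for a true difference between 0.90 and 0.95 SD. If 20% of patients were lost (16 per arm, an assumption), power at d = 0.5 would fall to 26%.

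**Precision of the difference.** The 95% half-width in SD units is t(0.975, 38) × √(2/20) = 2.024 × 0.316 = 0.64. An observed difference of zero would have an interval of about −0.64 to +0.64 SD, which includes d = 0.5 in either direction.

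**Precision of the SD.** On 38 degrees of freedom the 95% limits are √(38/χ²) times the estimate, which gives 0.817 and 1.289, or about −18% and +29%. A later sample size is proportional to SD², so its limits are 0.817² = 0.67 and 1.289² = 1.66 times the point calculation.

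**The case against.** The strongest reply is that this is a feasibility pilot. Its primary endpoint is safety and tolerability, its main analyses are descriptive, and it needs no power for efficacy. The Background also speaks more softly of a signal of efficacy. All of that stands, and nothing here calls for more patients. It does not rescue the stronger claim made in Sample size and repeated in Statistical analysis.

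It is also fair that the count of 19 draws partly on illustrative lists and that gait measures are correlated, so 62% is an upper figure for that count. That is why a range is given. Its lower end, 28%, is still more than five times 5%.

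Four stronger readings are tempting and should be resisted:
- **That there is no lead outcome.** The Gait section and the objectives name two. The gap is that they are not carried into the test.
- **That the tests will be unadjusted at 0.05.** The article is silent, and an analysis plan that is not shown may settle it. The 0.05 used here is an assumption.
- **That 40 patients cannot support power calculations.** They can: the SD will be estimated with a known margin.
- **That the earlier single-dose pilot's p-value supplies an effect size to judge power against.** The article gives no SD, arm sizes or test for that result, and it concerned one dose measured immediately, not 12 weeks of use.

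Nor does the abstract contradict the analysis section outright. It does not say that the secondary outcomes will only be described. It leaves the comparison out.

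**Conclusion.** The point holds as a mismatch between claim and design. Trial size borrowed from another study does not establish proof of concept, and the comparison meant to do so is spread over gait and cognitive outcomes in general, not tied to the two named as the focus. Under the assumptions stated, that raises the chance of some nominally positive finding from 8–10% to roughly 28–62%. At the same time a moderate true effect would be missed about two times in three on any one outcome. The trial can look for a preliminary signal and supply an SD for planning. The concern is with secondary analyses and leaves the safety, tolerability and feasibility aims untouched. It is worth correcting because it changes what the trial may conclude at almost no cost.

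**What to change.** 1. **Statistical analysis.** Base the proof-of-concept comparison on the 12-week change in step length variability and step time variability only. Report the between-arm estimates with 95% confidence intervals. Label all other gait and cognitive comparisons exploratory.
2. **Sample size.** Replace the claim to establish proof of concept with a statement such as: 40 patients will give a preliminary signal, with a 95% confidence interval of about ±0.64 SD for the between-arm difference, and will estimate the SD to within about −18% and +29%; the definitive trial will be sized from that SD, allowing for its uncertainty, and from a separately justified target difference. If losses are expected, quote these figures for the number expected to complete.
3. **Abstract, Design.** Mention the between-arm comparison, so that it agrees with the analysis section.

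The cost is wording in three places and a more modest claim. No patients, visits or measurements are added.

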### Assessment procedures

All patients will be assessed while in an ‘on’ motor state, taking their medication as prescribed. Participants will undergo a baseline visit to assess study eligibility by a clinician ([name]). This will include a detailed clinical review to encompass demographic and anthropometric data, falls history and medication. This clinical review will additionally include haemodynamic and autonomic function assessment including a 12-lead electrocardiogram (ECG) recorded using a bedside monitor. The ECG will be scrutinised by a clinician ([name]) for cardiac abnormalities. Haemodynamic parameters including heart rate, systolic and diastolic blood pressure will be recorded. In addition, five minutes of artefact-free R-R (beat-to-beat) interval data will be recorded. Quantitative markers of autonomic activity – both in time and frequency domains – will be computed according to the Task Force of the European Society of Cardiology [37], including heart rate variability (HRV).

Health-related quality of life, depression, global cognition and motor evaluation will be assessed using the Parkinson’s Disease Questionnaire (PDQ-39) [38], Geriatric Depression Scale-15 (GDS-15) [39], the Montreal Cognitive Assessment (MoCA) [40] and the MDS Unified Parkinson’s Disease Rating Scale III (MDS-UPDRS III) [41] plus Hoehn and Yahr staging [29], respectively. Hand grip strength will be measured with a Jamar handheld hydraulic dynamometer (Promedics, UK) acquiring three trials bilaterally following a standard protocol [42]. Furthermore, we will employ the Clinical Frailty Scale (CFS) [43] to estimate frailty status in the two weeks before assessment; the Gastroparesis Cardinal Symptom Index (GCSI) [44] to explore the impact of nVNS on gastroparesis symptoms; the Late-Life Function & Disability Instrument (LLFDI) to measure deficits in function and disability [45]; and the Functional Assessment of Chronic Illness Therapy-Fatigue Scale (FACIT-Fatigue) [46–48] to monitor fatigue.

### Primary outcome measures

We will primarily be examining the safety of the intervention in PwP and device tolerability by recording all adverse events reported by patients. Also, the proportion of eligible patients who agree to participate in the trial and the proportion of enrolled patients who successfully complete follow-ups will be monitored. During study visits, we will ask the participants to report any issues with using the device.

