## Materials and methods

### Study design

The study is a single-site, proof-of-concept, double-blind sham-controlled randomised pilot trial in patients with PD. Our trial will follow the Standard Protocol Items: Recommendations for Interventional Trials (SPIRIT) guidelines [26, 27]. The study comprises a baseline assessment visit (t_1_) followed by a 12-week treatment phase that includes remote monitoring of ambulatory activity and falls with monthly follow-up calls (t_2_ and t_3_). All participants will be invited for two follow-up visits at 12 weeks (t_4_) and 24 weeks (t_5_) with the latter to assess any long-term retention. At the end of the study, a subset of participants will be invited to contribute to a focus group discussion, to facilitate the shape of a future trial. Table 1 illustrates the SPIRIT flow diagram summarising all study procedures and outcome measures, randomisation, assessments, and interventions for each phase of the study.

**Table 1 Tab1:** SPIRIT flowchart. Abbrv. TAU, treatment as usual; MoCA, Montreal Cognitive Assessment; MDS-UPDRS-III, Movement Disorder Society-Unified Parkinson’s Disease Rating Scale Part III; H&Y, Hoehn and Yahr staging; PDQ-39, Parkinson’s Disease Questionnaire-39; GDS, Geriatric Depression Scale; CFS, Clinical Frailty Scale; GCSI, Gastroparesis Cardinal Symptom Index; LLFDI, Late-Life Function & Disability Instrument; FACIT-Fatigue, Functional Assessment of Chronic Illness Therapy-Fatigue; SRT, Simple Reaction Time; CRT, Choice Reaction Time; TMT, Trail Making Test; CANTAB, Cambridge Neuropsychological Test Automated Battery; OTS, One Touch Stockings; PAL, Paired Associative Learning

	STUDY PERIOD						
	Enrolment	Allocation	Post-allocation				Close-out
TIMEPOINT	-t_1_	0	t_1_ Start	t_2_ 4weeks	t_3_ 8 weeks	t_4_ 2 weeks	t_5_ 24 weeks
ENROLMENT							
Eligibility screen by care team	X						
Informed consent	X						
Balanced randomisation		X					
Allocation		X					
INTERVENTIONS:							
Active nVNS plus TAU		X					
Sham nVNS plus TAU		X					
ASSESSMENTS							
Questionnaires:							
MoCA			X				
MDS-UPDRS III & H&Y			X			X	X
PDQ-39			X			X	X
GDS-15			X				
CFS (v2.0)			X				
GCSI			X			X	X
LLFDI			X			X	X
FACIT-Fatigue			X			X	X
Device tolerability							X
Neuropsychological tests							
SRT			X			X	X
CRT			X			X	X
Digit vigilance			X			X	X
TMT A & B			X			X	X
CANTAB OTS			X			X	X
CANTAB PAL			X			X	X
Physical assessments							
Hemodynamic & autonomic function			X			X	X
Whole blood sample			X			X	

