### Trial design

The AdVaNSING-PD project is designed as a single-site randomised double-blind sham-controlled feasibility trial with two parallel groups and a primary endpoint of safety and tolerability after 12 weeks of self-administered nVNS with additional follow-up at 24 weeks to assess any carryover effects.

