**Fig. 1 Fig1:**
[figure not shown]
ElectroCore’s gammaCore nVNS device (left) and demonstrated use (right) with the device applied to the left side of the neck

Participants in both arms will be shown how to deliver the intervention at the Clinical Ageing Research Unit (Newcastle University) by an unblinded trainer after the participant’s eligibility has been confirmed and randomisation has occurred. The stimulation intensity will be controlled using the device control buttons and ramped up to a comfortable level of intensity. In addition to visual instructions, all participants receive a detailed instruction sheet on how to use the device. Participants will be phoned at weeks 4 and 8 to check progress. Following the 12-week treatment phase, participants will stop using the device, after they have additionally demonstrated their final stimulation to the assessor at the 12-week visit. This is followed by completion of the device tolerability and user questionnaire. Assessors will remain blinded.

The risk associated with the use of the gammaCore® nVNS device is minimal, and the safety profile is strong. The most common adverse events reported include local site tingling, pain, redness or itching and occur in approximately 17% of participants [34]. These adverse events are quickly resolved following discontinuation of the use of the device. Due to the theoretical risk of increased cardiac adverse events with stimulation of the right VN, participants will be asked to stimulate the left side [35]. Any adverse events (AE) will be diarised during the intervention and closely monitored until resolution, stabilisation or until it has been shown that the study procedures are not the cause. Participants who discontinue or deviate from the intervention protocol will be retained in the study as intention to treat.

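### The primary safety outcome is worded as adverse events that patients report, and the heart rate and blood pressure measurements scheduled at baseline, 12 and 24 weeks have no stated role in it

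*Protocol article*

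**What the plan says.** The Trial design section sets "a primary endpoint of safety and tolerability after 12 weeks of self-administered nVNS". The Primary outcome measures section gives the source of the data: "device tolerability by recording all adverse events reported by patients". The one other device-related input there is also self-report: "During study visits, we will ask the participants to report any issues with using the device". The section's remaining items are two feasibility proportions, participation and completion of follow-up.

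The Assessment procedures section describes a baseline clinical review with "haemodynamic and autonomic function assessment including a 12-lead electrocardiogram (ECG) recorded using a bedside monitor", and adds: "Haemodynamic parameters including heart rate, systolic and diastolic blood pressure will be recorded". Table 1 has a row named "Hemodynamic & autonomic function", marked at t1, t4 and t5.

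On risk, the Intervention section explains the choice of the left side by the "theoretical risk of increased cardiac adverse events with stimulation of the right VN". On event capture, it says: "Any adverse events (AE) will be diarised during the intervention and closely monitored until resolution".

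**The concern.** Changes in heart rhythm, heart rate or blood pressure need not be felt. The trial checks for them objectively at entry: the eligibility criteria use an ECG and repeated blood pressure readings, and exclude clinically significant hypotension, bradycardia and tachycardia. During treatment, the primary safety outcome relies in its wording on what participants say.

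Taken literally, an unfelt fall in blood pressure or heart rate found at the 12-week visit would lie outside the primary safety outcome and could appear only as a change in autonomic function. This matters because safety is the trial's primary conclusion. The Discussion section says that the device's safety and tolerability in PD have not been formally investigated, least of all with repeated dosing, and that the results will inform a larger multi-centre trial.

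**Working it through.** The article states no figure that bears on this point. The sample size of 40 is justified by precedent, with no event rate or precision. The check is therefore mainly a comparison of sections.

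**1. What feeds the primary safety outcome.** Primary outcome measures names adverse events reported by patients and device issues reported by participants. It names no measured quantity and no event detected by staff.

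**2. What is measured, and when.** The haemodynamic and autonomic row of Table 1 is marked at t1, t4 and t5. The Study design text gives t4 as 12 weeks and t5 as 24 weeks. The table header prints t4 as 2 weeks, which looks like a slip.
- Heart rate and blood pressure: described in Assessment procedures as recorded. Their repetition at follow-up rests on the Table 1 row.
- 12-lead ECG: described within the baseline eligibility review, as part of the assessment that shares the row's name. The row does not name the ECG, so a repeat at t4 and t5 is an inference.

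**3. What role these data are given.** The abstract lists autonomic function among the secondary outcomes, as an improvement. The Discussion section likewise speaks of improvement in autonomic function. Statistical analysis compares change scores between groups for gait and cognition and summarises outcome data descriptively. No section assigns heart rate, blood pressure or ECG to the safety outcome.

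**4. Whether another section closes the gap.**
- The abstract says adverse events will be recorded, without limiting the source.
- The Intervention section has events kept in a diary and followed up, including until study procedures are shown not to be the cause.
- Table 1 schedules adverse events at every assessment from t1 to t5.
- The Discussion section links clinical, digital and laboratory data jointly to safety, tolerability, feasibility and potential effectiveness.

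All four are wider than the primary outcome wording. None says that an unfelt abnormality found at a visit counts towards the primary safety outcome.

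**5. Illustration of size, on assumed rates.** With 40 participants at 1:1, each arm has 40 / 2 = 20. If a proportion *p* of the active arm had an unfelt abnormality, independently, the chance of at least one is 1 − (1 − *p*)^20.
- *p* = 5%: expected number 20 × 0.05 = 1; 1 − 0.95^20 = 1 − 0.358 = 0.642.
- *p* = 10%: expected number 20 × 0.10 = 2; 1 − 0.90^20 = 1 − 0.122 = 0.878.

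These rates have no basis in the documents. With no background rate for the sham arm, the figures say nothing about harm caused by stimulation. They show only that a pilot of this size could hold such a case.

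**The case against.** The strongest answer is that the phrase about patient reports is loose drafting in a summary sentence. The sections listed in step 4 are broader, and nothing prevents an investigator from logging an abnormal reading as an adverse event. Definitions of adverse events, sources of detection and safety tables commonly sit in a full protocol or analysis plan, which are not shown. Autonomic measures will in any case be summarised, so a group-level shift would be visible under some heading.

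Much of this stands. A reader might infer that safety rests *only* on patient report, or that a silent finding *would not* be counted; the documents do not support either, because the wider wording leaves room to log it. A reader might also take it that an ECG is recorded at 12 and 24 weeks; the article does not say so. Nor do the documents make cardiac harm the main expected risk. The cardiac risk they name is theoretical and tied to right-sided stimulation, which the trial avoids. They call the device risk minimal, and the common events they list are local to the stimulation site.

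The objection does not remove the point. The absence of safety tables from an article is no finding. What is at issue is the source of primary safety data that the article does state. That wording is narrower than the rest of the article and leaves scheduled measurements without a safety role. A group-level summary of autonomic function also does not show how many participants had a clinically significant change.

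**Conclusion.** The point holds as a matter of wording and outcome definition. The primary safety outcome is stated in terms of patient-reported events, while heart rate and blood pressure (and an ECG, if repeated) are scheduled at 12 and 24 weeks with no named role beyond autonomic improvement. The broader statements elsewhere permit unfelt abnormalities to be counted but do not provide for it, so the safety conclusion could be drawn without objective data the trial already holds.

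The size cannot be derived from the documents. The 64% to 88% range depends wholly on assumed rates of 5% to 10% and on 20 participants per arm. The conclusion also assumes that the Table 1 row at follow-up includes the heart rate and blood pressure described for that assessment. It does not depend on a repeated ECG. Sample size and treatment are unaffected.

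**What to change.** In Primary outcome measures, define the events as *adverse events reported by patients or detected at study assessments*. As part of the safety reporting, give by arm at t4 and t5:
- the change from baseline in heart rate and in systolic and diastolic blood pressure;
- the number of participants with a new abnormality judged clinically significant by a clinician blind to arm.

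State whether the 12-lead ECG is repeated at t4 and t5, and include its findings in this reporting if it is.

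The entry exclusions should not be reused unchanged as event criteria. The blood pressure exclusion calls for three measurements within 24 hours, which Table 1 does not show at follow-up, and some ECG examples are items of history rather than new findings.

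The cost is one reworded sentence, one clarification and one table from assessments already scheduled. No new visit is needed. The small downside is a few more events to adjudicate in both arms.
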